### Procedures

#### Randomization

For feasibility, the trial will occur in three cohorts. Randomization will occur at the beginning of each planned cohort. If possible, we will stratify the practices in each cohort by Medicaid rate before randomizing. Randomization will be conducted by the project’s data manager using random number generation in SAS. Practices will be informed of randomization after baseline data collection is completed. Research staff who have contact with participants will be unaware of implementation condition.

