#### Caregiver recruitment and screening

Caregivers of children visiting the practice will be informed about the study using multiple methods (e.g., posters, brochures, PCP referral). Recruitment materials, available in English and Spanish, direct caregivers to their PCP and a website with more information and a short orientation video. Caregivers complete an online screening process. Eligible caregivers will then be given login credentials to access and complete an online consent and the baseline assessment via a smartphone, tablet, or computer. Caregivers who cannot read or write and caregivers without a smartphone or computer are directed to call the study coordinator to complete the screening and consent process.

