### Statistical analyses

#### Aim 1

Our primary analytical tool for Aim 1 will be a two-way analysis of variance with interaction using mixed-effects linear models for continuous outcomes and generalized linear mixed models for categorical variables. We will use an intent-to-treat approach. We will examine patterns of missingness and, if necessary, use imputation methods using available covariates [141, 142]. For exploratory analyses, we will use variable selection methods such as Lasso and elastic net to get parsimonious models that fit well. Analyses will be conducted at the end of the trial; no interim analyses are planned.

For implementation outcomes, we hypothesize that relative to REP only, TEAM, LEAD, and their interaction will significantly improve (1) the number of DOCC service encounters per case and (2) collaborative care competencies within the practice. We will test effects on outcomes at months 6, 12, 18, and 24. Fixed effects include time, condition, and practice, and random effects will account for nesting. We will conduct planned contrasts to test differences between conditions.

For patient outcomes, we hypothesize that relative to REP only, TEAM, LEAD, and their interaction will significantly improve (1) child symptom severity and (2) quality of life. Fixed effects include time and condition, and random effects will account for nesting. As exploratory analyses, we will run larger models adjusting for demographic and baseline clinical variables and assess goodness of fit.

#### Aim 2

We hypothesize that TEAM practices will show significant gains in our proposed TEAM targets (team functioning, integration/quality) and that LEAD practices will show significant gains in our proposed LEAD targets (implementation leadership, implementation climate). We will use larger models to adjust for demographic and baseline clinical variables, test goodness of fit, and compare different time periods to check model fit. We will test if the association between each condition (TEAM, LEAD) and each implementation outcome is mediated by their respective targets and explore serial mediation.

#### Aim 3

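### The main child-outcome model leaves the month-0 score to exploratory analyses, which costs precision that data already collected would supply

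*Protocol article*

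**What the plan says.** All references are to the protocol article.

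- **Statistical analyses, Aim 1, patient outcomes.** The model is described in one sentence: "Fixed effects include time and condition, and random effects will account for nesting". The next sentence assigns baseline adjustment a different status: "As exploratory analyses, we will run larger models adjusting for demographic and baseline clinical variables and assess goodness of fit".
- **Statistical analyses, Aim 1, implementation outcomes.** The list is longer: "Fixed effects include time, condition, and practice, and random effects will account for nesting".
- **Professional and caregiver assessments, and Table 2.** The parent and teacher Vanderbilt scales and the PEDS-QL are scheduled at months 0, 3, 6 and 12, so each child outcome has its own baseline value. Aim 1 describes the clinical outcome as change in symptom severity and classes it as secondary.
- **Randomization.** There are three cohorts: "Randomization will occur at the beginning of each planned cohort". Stratification is conditional: "If possible, we will stratify the practices in each cohort by Medicaid rate before randomizing". On disclosure: "Practices will be informed of randomization after baseline data collection is completed".
- **Caregiver recruitment and screening.** Families learn of the study at the practice by several routes, among them "posters, brochures, PCP referral".

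**The concern.** The month-0 score of a symptom or quality-of-life scale is usually the strongest available predictor of its later value. A main model without it carries child-level variance that could be removed, and here the plan assigns such adjustment to exploratory work. This is a stated choice, and an analysis plan that follows the article would inherit it.

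The trial randomizes 24 practices and recruits children within them. A primary care provider who knows the practice's condition may refer different families, so baseline severity could differ between conditions through selection as well as chance. A model of follow-up scores without the baseline score would carry part of that difference into the treatment contrast.

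At stake are the power and the robustness of the clinical comparison. The primary outcome, the number of encounters per case, has no baseline value and is not affected by the month-0 symptom point.

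**Working it through.** **Inputs from the article.** Up to 600 caregivers (24 × 25); 20% attrition and ICC 0.01 among cases treated by the same provider (Power and sample size); mean 4.4 providers per practice; stated detectable effect 0.25 with 262 cases per condition.

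**Assumptions.** Two-sided alpha 0.05; 80% power for patient outcomes (the article states 80% only for the primary outcome); r, the correlation between month-0 and follow-up scores, from 0.3 to 0.7.

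**1. The plan's own figure.** With SD 1, an effect of 0.25 needs 252 per group. With 5 cases per provider (assumed), the design effect is 1 + (5 − 1) × 0.01 = 1.04, and 252 × 1.04 = 262.1. Without clustering, 262 per group gives power 0.816. The stated figure reproduces with no baseline adjustment.

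**2. Variance relative to the baseline-adjusted model, one follow-up visit.** Variance factors are 1 for follow-up only, 2(1 − r) for change from month 0, and 1 − r² with the month-0 score as covariate.

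| r | Follow-up only, 1/(1 − r²) | Change score, 2/(1 + r) |
|---|---|---|
| 0.3 | 1.10 | 1.54 |
| 0.5 | 1.33 | 1.33 |
| 0.7 | 1.96 | 1.18 |

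Both alternatives are less precise at every r shown. The direction does not depend on r; only the size does.

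**3. Detectable main effect, ICC within provider as stated.** Retained per factor level: 600 × 0.8 / 2 = 240. Retained cases per provider: 20/4.4 = 4.55, so the design effect is 1 + 3.55 × 0.01 = 1.0355. Unadjusted: (1.960 + 0.842) × √(2 × 1.0355/240) = 0.260. Multiplying by √(1 − r²):

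| r | Detectable effect, adjusted | Power at 0.25 (unadjusted 0.77) |
|---|---|---|
| 0.3 | 0.248 | 0.81 |
| 0.5 | 0.225 | 0.87 |
| 0.7 | 0.186 | 0.96 |

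The change-score model gives 0.308, 0.260 and 0.202 at the same three values of r.

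**4. Sensitivity: ICC 0.01 applied at practice level, 20 df.** With 20 retained children per practice, the variance of a practice mean is 0.01 + 0.99/20 = 0.0595. With 12 practices per level and 20 df (24 − 4), the sum of t quantiles is 2.946, and 2.946 × √(2 × 0.0595/12) = 0.293. If adjustment shrinks only the child-level part, at r = 0.5 the variance is 0.01 + 0.0495 × 0.75 = 0.0471, and 0.293 × √(0.0471/0.0595) = 0.261. At r = 0.6 it is 0.01 + 0.0495 × 0.64 = 0.0417, giving 0.246.

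**5. Imbalance.** In a follow-up-only model, a baseline difference d shifts the contrast by r × d. For an illustrative d = 0.2 SD, the shift is 0.06, 0.10 or 0.14 SD at r = 0.3, 0.5 or 0.7, against the plan's 0.25. Chance alone gives a main-effect baseline difference with SD √(2 × 1.0355/240) = 0.093.

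**6. Cost of the design factors.** Three cohorts use 2 df and a two-level Medicaid stratum (assumed) uses 1, so df go from 20 to 17. The t critical value goes from 2.086 to 2.110 and the quantile sum from 2.946 to 2.973. Step 4 at r = 0.5 becomes 0.261 × 2.973/2.946 = 0.264. What these terms gain cannot be computed from the article.

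**The case against.** The strongest reply is that a condensed article lists what its models include without claiming completeness. The clinical outcome is change and month 0 is measured, so the mixed model may already take month 0 as a response and compare change between conditions; imbalance would then be largely differenced out. Baseline clinical variables also need not mean the outcome's own month-0 score. These points weaken the imbalance argument but not the precision argument: an unconstrained change comparison still has 2/(1 + r) times the variance, and nothing in the article names the month-0 score as a covariate or a constrained response.

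A reader might infer three stronger things that the article does not support.

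- **That cohort and Medicaid stratum are in no model.** The implementation-outcome model has practice as a fixed effect, and each practice belongs to one cohort and one stratum, so that term contains both. Adding them there as well would be collinear. Stratification is itself conditional.
- **That a condition term without condition-by-time dilutes the effect, from 0.25 to 0.19 (three of four visits, a factor of 0.75).** This needs month 0 to be an outcome row with no time-specific contrast. The article states neither, and this reading cannot hold together with the follow-up-only loss.
- **That recruitment imbalance will occur.** Enrolment after disclosure is a reasonable inference, but the article does not say whose baseline data must be complete before practices are told. Eligibility uses a fixed PSC-17 cutoff, screening is online, and research staff in contact with participants are unaware of condition. Adjustment would remove only imbalance carried by measured variables.

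**Conclusion.** The point holds for the main child-outcome model. As described, it leaves baseline adjustment to exploratory analyses and is less precise than a model with the month-0 score, whether it analyses follow-up scores or change. At an assumed r of 0.5 the variance is a third larger either way. The detectable main effect would fall from about 0.26 to 0.225 with the ICC within provider, or from 0.29 to about 0.26 with the ICC at practice level. Over r = 0.3 to 0.7 the within-provider result runs from 0.25 to 0.19. The size rests on r, which the article does not give, and on the assumed alpha and power.

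Protection against baseline imbalance is a second, unquantified benefit. Because these outcomes are secondary, this is a worthwhile improvement to the analysis and not a threat to the trial's primary conclusion.

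**What to change.** In the main model for each child outcome, include that outcome's month-0 score, in one of two forms:

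- as a covariate, with the follow-up visits as responses; or
- as a response constrained to a common month-0 mean across conditions, with the treatment effect read from a stated condition-by-time contrast.

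Keep only the wider demographic models exploratory. In the same child-outcome model, add randomization cohort and, if stratification is carried out, the Medicaid stratum. Leave the implementation-outcome models without these two terms while practice is a fixed effect there.

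The cost is a change of analysis wording before outcome data are examined by condition, no new data collection, and about three between-practice degrees of freedom if the stratum has two levels (t critical value from about 2.09 to 2.11).

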## Current study

We propose to disentangle and further refine facilitation strategies targeting the care team and leadership levels to support implementation of a CCM in pediatric primary care. We will conduct a cluster-randomized, hybrid type 3 effectiveness–implementation trial [85] using a 2 × 2 factorial design to test the main and interactive effects of implementation strategies that target the care team level (TEAM) or leadership level (LEAD) on implementation and clinical outcomes. All practices will first receive standard implementation strategies based on the Replicating Effective Programs (REP) model [86]. Practices then will be randomized to four conditions: (1) Standard REP only; (2) TEAM, (3) LEAD, and (4) TEAM + LEAD.

Standard REP is a low-cost and low-burden strategy consisting of a tailored intervention manual, didactic training, and brief technical support [87–89]. REP is based on the Centers for Disease Control and Prevention’s Research-to-Practice Framework [86, 90, 91] and derived from Social Learning Theory [92] and Rogers’ diffusion model [93]. It is easily scalable in most community-based practices. Although standard REP only may help some sites to adequately adopt an EBP, evidence suggests it is unlikely to be sufficient in many lower-resourced settings, and augmentations to REP may be necessary [53]. In this study, we will evaluate the effects of augmenting REP with two different types of facilitation (TEAM and LEAD) targeting different levels, audiences, and mechanisms.

TEAM facilitation is informed by existing approaches to facilitation, including external facilitation [52, 53, 67], practice facilitation [62, 64, 94, 95], and coaching [63, 64], in which an outside expert helps providers improve EBP uptake. TEAM also incorporates strategies from team development interventions (i.e., team building [96, 97], team training [98, 99], debriefing [100, 101]) to improve care team functioning and effectiveness. TEAM aims to improve implementation outcomes by targeting provider clinical competencies, team functioning, and team integration/quality.

LEAD is based on the Kirchner [67] and Kilbourne et al. [102] internal facilitation role. It focuses on reducing organizational barriers to implementation by promoting practice champions who sustain the EBP. LEAD aims to improve implementation outcomes by targeting implementation climate [77, 103, 104] and implementation leadership [105, 106].

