#### Aim 2: test for target engagement in each implementation condition and if hypothesized mechanisms mediate the effects of TEAM and LEAD on implementation outcomes

Our hypothesized mechanisms for TEAM are team functioning and effectiveness; hypothesized mechanisms for LEAD are implementation leadership and implementation climate. We hypothesize that each condition will have main effects on one or both of its targets. We also expect that the effects of TEAM and LEAD on outcomes will be mediated by their hypothesized targets.

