### Implementation conditions and strategies

The four implementation conditions are shown in Fig. 1. Table 1 lists the mechanisms of change at the individual, team, and practice levels targeted by each condition. Supplemental File 3 shows the ERIC implementation strategies included within each condition and their hypothesized mechanisms of action (Supplemental Table 1) and the specific actions within each condition (Supplemental Table 2).

**Table 1 Tab1:** Implementation conditions and targets by level

Level	Implementation condition	Target/mechanism
Individual provider	Standard REP	Self-efficacy
		Attitudes
Care team	TEAM facilitation	DOCC skill
		Fidelity
		Affective, behavioral, and cognitive functioning
		Team effectiveness
Practice	LEAD facilitation	Implementation climate
		Implementation leadership

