#### Care team facilitation (TEAM)

TEAM is a phased approach designed to improve providers’ skill in using DOCC, teamwork quality, and team effectiveness. The TEAM facilitator is a licensed clinician who delivered DOCC in a prior trial and has lived experience as a consumer of integrated care for a child with ADHD. TEAM facilitation will occur via a graded schedule of videoconference calls over 18 months (weekly to bimonthly).

In the first phase of TEAM, the facilitator will engage the care team in identifying barriers and facilitators, enhancing motivation to use DOCC, and setting goals for implementation in their practice. The second phase focuses on reviewing and revising roles, responsibilities, and workflows within the team to improve collaboration, coordination, and use of DOCC. As part of this phase, the facilitator will support the team in developing effective communication and problem-solving skills. The third phase focuses on increasing the team’s competency and fidelity to DOCC through ongoing training in treatment content (e.g., didactics, modeling, role plays), structured reviews of patient progress, audit and feedback on use of the patient registry, consultation on challenging cases, and support in overcoming barriers and balancing model adaptations and fidelity. The last phase of TEAM focuses on the team’s capacity to sustain and continually improve DOCC in their practice. The facilitator will conduct structured team debriefings and encourage the team to identify and address potential problems in team processes. The facilitator will also guide the team in reflecting on implementation, reviewing and revising implementation goals, and planning for sustainability and continuous quality improvement.

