##### Fidelity to DOCC

Fidelity to DOCC will be documented in two ways. First, we will evaluate dosage for all cases. We define adequate dosage as at least 6 DOCC encounters and at least 1 care management meeting for each case [137, 138]. Second, we will assess fidelity by reviewing audio recordings of DOCC treatment sessions. CMs will upload two session audio recordings for cases that consent to recording via a secure, HIPAA-compliant audio portal. A trained research assistant (unaware of implementation condition) will rate recordings using the Treatment Integrity Rating Form [139].

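### Aim 2 omits DOCC skill and fidelity, which the protocol itself names as TEAM mechanisms, so an effect through team functioning could not be told apart from clinical coaching

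*Protocol article*

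**What the plan says.** All references are to the protocol article.

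Three places include clinical skill or fidelity among the things TEAM is meant to change:

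- **Table 1**, under Implementation conditions and strategies, is introduced with "Table 1 lists the mechanisms of change at the individual, team, and practice levels targeted by each condition". Its TEAM rows are DOCC skill, fidelity, team functioning (affective, behavioral and cognitive) and team effectiveness.
- **Current study**: "TEAM aims to improve implementation outcomes by targeting provider clinical competencies, team functioning, and team integration/quality".
- **Care team facilitation (TEAM)**, on the third of four phases: "The third phase focuses on increasing the team’s competency and fidelity to DOCC through ongoing training in treatment content".

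Three places set out what Aim 2 tests, and none includes skill or fidelity:

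- **Aim 2 in Study aims**: "Our hypothesized mechanisms for TEAM are team functioning and effectiveness".
- **Table 2, Aim 2 mediators**: for TEAM, the staff survey of team functioning (PCTDS, with the TDM as secondary measure) and the caregiver survey of team integration/quality (PICS).
- **Statistical analyses, Aim 2**: "TEAM practices will show significant gains in our proposed TEAM targets (team functioning, integration/quality"). Mediation is then tested through each condition's own targets, and serial mediation is to be explored with no variables named.

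Fidelity is nevertheless measured. The section Fidelity to DOCC gives two measures: a dosage criterion (at least 6 encounters and at least 1 care management meeting per case), and ratings of recorded sessions by an assistant unaware of condition. On the recordings it says "CMs will upload two session audio recordings for cases that consent to recording". Neither measure is assigned to an aim.

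**The concern.** TEAM is a bundle: it coaches clinical skill and it develops the team. Randomizing practices to TEAM estimates the effect of the whole bundle and cannot show which part did the work. Within this design only the Aim 2 mediator analysis speaks to that, and it contains one part of the bundle and not the other. Both LEAD mechanisms in Table 1 are carried into Aim 2; two of the four TEAM mechanisms are not.

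The Background presents the trial as a way to look inside the black box of facilitation. If the plan is followed as written, the trial could report that TEAM works through team functioning when some or all of that path reflects clinical coaching. Equally, a skill effect could sit in the direct effect with nothing in the analysis to identify it. Either result would steer later users of the strategy on which part of TEAM to keep.

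**Working it through.** **1. The TEAM mechanism lists side by side**

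| Place in the article | Skill / competency | Fidelity | Team functioning | Effectiveness or integration/quality |
|---|---|---|---|---|
| Current study | yes | – | yes | yes |
| Table 1 | yes | yes | yes | yes |
| TEAM, third phase | yes | yes | – | – |
| Aim 2 in Study aims | – | – | yes | yes |
| Table 2, Aim 2 mediators | – | – | yes | yes |
| Statistical analyses, Aim 2 | – | – | yes | yes |

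**2. Whether another planned measure fills the gap**

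- Dosage is counted from the same encounters that form the primary outcome, so it cannot serve as a mediator of that outcome.
- The MHPRI rates care management functions at practice level and is itself an implementation outcome.
- The training quizzes belong to Standard REP, which every practice receives, and are not listed as a mediator.
- The session rating is the remaining candidate.

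**3. What omitting skill does to the mediation estimate**

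The documents give no path values, so everything in this step is assumed. Let TEAM raise skill by a_S and team functioning by a_T (in within-condition SDs). Let skill have slope b on the outcome, functioning have no effect on it, and the two correlate at r within condition.

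- Total TEAM effect = a_S × b
- Coefficient of functioning when skill is left out = r × b
- Indirect effect credited to functioning = a_T × r × b (true value 0)
- Share of the total = (a_T × r × b) / (a_S × b) = a_T × r / a_S

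The slope b cancels from the share. With a_S = 0.8 and b = 0.5, the total is 0.8 × 0.5 = 0.40. The credited indirect effect and its share are:

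| a_T | r = 0 | r = 0.3 | r = 0.5 | r = 0.7 |
|---|---|---|---|---|
| 0 | 0 (0%) | 0 (0%) | 0 (0%) | 0 (0%) |
| 0.4 | 0 (0%) | 0.06 (15%) | 0.10 (25%) | 0.14 (35%) |
| 0.8 | 0 (0%) | 0.12 (30%) | 0.20 (50%) | 0.28 (70%) |

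The remainder of the 0.40 appears as direct effect.

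A smaller setting gives the same pattern. With a_S = a_T = 0.5, b = 0.4 and r = 0.5, the total is 0.5 × 0.4 = 0.20 and the credited indirect effect is 0.5 × 0.5 × 0.4 = 0.10, again half.

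**4. Check by simulation** (400,000 units, a_S = a_T = 0.8, b = 0.5, r = 0.5)

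- Functioning alone: indirect 0.20, direct 0.20.
- Skill and functioning together: 0.00 through functioning, 0.40 through skill, 0.00 direct.

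The second line assumes skill is observed for every unit without selection. The trial's rating does not meet that condition, as set out in the next part.

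**The case against.** **The natural remedy is itself flawed.** A reader might infer that entering the fidelity rating beside team functioning would settle the mechanism. It would not. A rating exists only where sessions took place and the family agreed to recording. Cases with no sessions have none, and cases with few may lack two. The mediator is thus selected on the outcome it should explain, and the rated sessions are themselves among the counted encounters. There is no baseline rating, and with one care manager per practice the score is close to a variable with 24 units. This stands, and it limits the fix.

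**A TEAM effect would not be missed.** A reader might infer that a skill-driven benefit would go undetected. Aim 1 estimates the total TEAM effect whatever its path. Nor is a null mediation result wrong in itself: if skill were the true path, team functioning would rightly be unsupported.

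**The size is not established.** The range includes zero. A false positive mediation finding may also be rare: with 24 independent practices, the smaller setting above and a joint-significance test, simulation gave one in about 3% of trials. Larger effects or a staff-level analysis could raise that. The article itself says mediation has power for large effects only. This stands against any claim that misattribution is likely. It does not remove the bias in the estimate or reconcile the lists.

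**Care managers choosing their best sessions.** A reader might infer this because they upload the recordings. The article does not say who selects sessions, and a recording rule is operational detail it may leave to the full protocol. It is no part of this point.

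**More may be said elsewhere.** Supplemental File 3, to which the article refers for mechanisms, is not shown, and nothing in the article rules out comparing fidelity across conditions. But the article itself fixes the Aim 2 TEAM targets in three places, in conflict with its own Table 1, so this is not detail left open for an analysis plan.

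**Conclusion.** The point holds as a contradiction between the stated TEAM mechanisms and the mechanisms Aim 2 tests. Two of the four in Table 1, DOCC skill and fidelity, appear in neither the target-engagement nor the mediation tests as written.

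The consequence is confined to the mechanism conclusion. In the settings tried, between 0% and about 70% of a purely skill-driven effect is credited to team functioning. Two conditions are both needed for any misattribution: TEAM must move functioning, and functioning must correlate with skill. If either fails, the whole skill effect stays in the direct path. All path values are assumptions, so the range shows direction and possible scale and is not a forecast.

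This is worth correcting, at the level of a secondary aim. It leaves the primary comparison of encounters untouched.

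**What to change.** 1. Add the condition-masked Treatment Integrity Rating Form score to the TEAM targets in Aim 2 and Table 2. Test the TEAM effect on it by comparing conditions after baseline, since a change from baseline is not available.
2. State that dosage will not be used as a mediator of encounters, because it is built from the same encounters.
3. Label any model with the rating beside team functioning as an exploratory sensitivity analysis. Give the reason: ratings exist only for consenting cases with delivered sessions and so are selected on the outcome.
4. State in Aim 2 that an indirect effect through team functioning cannot be separated from clinical skill coaching, and word the mechanism conclusions accordingly.

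Cost: the ratings are already planned, so no new data collection is needed. The downside is one more exploratory test, limited to recorded cases, in a design with little power for mediation.
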